### Inclusion and Exclusion Criteria

General and specific inclusion and exclusion criteria for both PD patients and controls are reviewed below.

General criteria: (1) age 50 to 77 years to avoid early-onset PD and (2) no evidence of depression on the Beck Depression Inventory (BDI-II >18 is predictive in mild PD) [24].

PD criteria: (1) Diagnosis of idiopathic PD based on the presence of 2 cardinal features [25], (2) improvement with DRT, (3) minimal or mild disease severity based on the Hoehn and Yahr rating scale of <2.5 and motor UPDRS <30 *on* DRT medications [22], and (4) normal or MCI cognition based on MoCA screening (>21) at baseline [26].

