#### Connectivity Analysis

Following the preprocessing steps as described earlier, we will register all the 300 volumes collected for rs-fMRI to the first volume of the time series. As differential head motion between groups can introduce artifacts, we will equate the PD and control groups with a *scrubbing* procedure to remove volumes compromised by motion [53]. The resting-state series will then be registered to the high-resolution structural images, spatially normalized to standard space using the MNI atlas, and resampled to a spatial resolution of 2.0 mm isotropic and then spatially blurred using a 5-mm Gaussian kernel. The segmented masks (GM, WM, and CSF) created as part of the measurement for cortical atrophy will account for time series variance from the nonneuronal contributions of CSF and WM. In addition, the 6 standard movement parameters from registration will be regressed out of the 4-dimensional data. Graph-theoretic analysis on selected ROIs that are relevant to PD cognition based on our hypotheses will be performed and expanded to a more global approach using Graph Analysis Toolbox (GAT) [54]. The ROI method will consider regions such as *caudate, putamen, cingulate, orbitofrontal, dorsolateral prefrontal cortex (DLPFC), superior and inferior parietal, posterior and anterior visual cortex, superior and medial temporal.* Pairwise correlations between mean BOLD time series using ROIs will be utilized to create functional connectivity matrix followed by the Fisher transformation to z score association matrix. Various topological features of the networks will be captured at the global and regional level such as total connectivity, normalized clustering coefficient, normalized path length, density, global efficiency, and betweenness centrality [55]. Between-group comparisons will be made using a 2-sample *t* test after correcting for multiple comparisons with significance set at *P*<.05. To determine the relationship of the network topology with cognition, we will correlate all subtests of the neuropsychological and visuoperceptual assessments using the Pearson correlation coefficient comparing PD with normal cognition across 4 years and PD with cognitive progression.

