### Statistical Analysis and Power

A sample of 120 PD patients is planned for this study. On the basis of the experience of longitudinal studies in PD, the attrition (mortality and loss to follow-up) is anticipated at 16% for 4 years. Thus, initial recruitment of 120 patients will yield about 100 subjects after 4 years. On the basis of published data, we estimate 70% PD-NC and 30% PD-MCI patients in our sample, and conversion rates of 60% from NC to MCI and 80% from MCI to PDD after 4 years. One of our primary goals is to evaluate progression patterns to determine time-specific differences between groups (NC vs MCI at baseline and PDD vs MCI, MCI vs NC, and PDD vs NC at year 4). Our study will have 80% power to detect medium-to-large average differences across time between the different groups under various within-subject correlations. In terms of predictive models for 4-year outcomes, our study will have 90% power to detect at least 0.86 area under the receiver operating characteristics curve (AUROC) for PDD conversion and 95% power to detect at least 0.74 AUROC for MCI at year 4.

To study differential cognitive progression patterns, generalized estimating equations will be used for describing the longitudinal trajectories of neuropsychological and visuoperceptual performances between PD-NC and MCI groups comparing baseline performance with different time points. The model will provide estimates of PD-MCI versus PD-NC differences at specific time points and longitudinally. Covariates such as age, UPDRS, and visual illusions or hallucinations will be added to the model to enable determination of adjusted differences.

We will investigate the prognostic value of baseline cognition in predicting relative risk for progression to PDD through a multiple logistic regression model. The best combination of baseline measures and covariates included in the prediction model will be selected by the elastic net procedure. Summary statistics of the AUROC will be used to evaluate the predictive power. Sensitivity, specificity, positive predictive value, and negative predictive value will be calculated from the optimal threshold determined by the Youden index. The prediction models will be cross-validated by training and testing methodology.

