### Anatomical and Regional Brain Activation Patterns Predictive of Cognitive Progression

Significant atrophy has been associated with transition from MCI to AD [65,66]. However, there is limited work on cortical thinning in early PD, and no longitudinal studies have evaluated cortical thickness measures as biomarkers signaling rapid cognitive progression in PD [17,67]. Critically important to prediction is evaluating differences in patterns of cortical atrophy based on the timing of onset of cognitive progression. This could reveal an anatomical basis for the timing of cognitive decline, thus elucidating the pathological burden in PD [17].

There is an increased interest in studying resting-state brain networks to try and understand interactions between disparate brain regions. Rs-fMRI measures the strength of functional interactions between brain regions based on temporal correlations of the spontaneous fluctuations in the resting-state BOLD signal, such that synchronous temporal changes in signal are functionally connected [68]. Rs-fMRI has been used to test the efficiency and strength of large-scale neuronal networks in the absence of a task. Although rs-fMRI has revealed the natural history of amnestic MCI to AD, very little is known about its efficacy as a biomarker in PD [69,70]. Characterizing differences in PD will elucidate temporal changes in functional networks related to relative changes in frontal, medial-temporal, and posterior cortical regions with cognitive progression and provide neural insights into the timing of pathophysiological changes in PD.

Cortical thickness, voxel-based morphometry, and rs-fMRI will characterize the evolution of regional brain degeneration annually for 4 years in PD patients. We predict a higher rate of cortical thinning and decreased functional connectivity in occipito-parieto-temporal regions in PD patients with cognitive progression.

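### The network topology comparison sets always-normal patients against all progressors, so baseline cognitive status is confounded with progression and stable-MCI patients have no place

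*Protocol article*

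**What the plan says.** All references are to the protocol article.

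- **Connectivity Analysis.** To relate topology to cognition, "we will correlate all subtests of the neuropsychological and visuoperceptual assessments using the Pearson correlation coefficient", and the same sentence names the groups: "comparing PD with normal cognition across 4 years and PD with cognitive progression". No third group, baseline stratum or covariate for baseline cognitive status is stated.
- **Connectivity Analysis, preceding sentence.** "Between-group comparisons will be made using a 2-sample *t* test after correcting for multiple comparisons with significance set at *P*<.05". This sentence does not name its groups.
- **Inclusion and Exclusion Criteria.** Patients may enter with "normal or MCI cognition based on MoCA screening (>21) at baseline".
- **Statistical Analysis and Power.** "we estimate 70% PD-NC and 30% PD-MCI patients in our sample", with "conversion rates of 60% from NC to MCI and 80% from MCI to PDD after 4 years". The longitudinal model by baseline group in that section covers neuropsychological and visuoperceptual performance. The logistic model predicts PDD from baseline cognition. Neither is described for the network metrics.
- **Discussion, section on anatomical and regional brain activation patterns.** The expected result is worded in terms of progressors: "We predict a higher rate of cortical thinning and decreased functional connectivity in occipito-parieto-temporal regions in PD patients with cognitive progression".

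**The concern.** A patient who is normal at every visit is normal at baseline. A patient with cognitive progression may have started as NC or as MCI. Unless the progressor group is restricted in some unstated way, the two groups differ in baseline cognitive status by construction. The natural comparator for MCI-to-PDD, a patient who starts and stays MCI, belongs to neither group.

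The study wants markers that come before conversion. A network feature that only tracks being MCI already would be more common among these progressors than in the reference group. It could also produce a topology-cognition correlation among progressors simply because two baseline classes are mixed there. Either result could be read as support for the hypothesis of reduced connectivity in progressors when it carries no information about who will progress.

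**Working it through.** **Inputs.** From Statistical Analysis and Power: 120 recruited, 16% attrition, baseline mix 70% NC and 30% MCI, conversion 60% (NC to MCI) and 80% (MCI to PDD). The article gives no effect size for network metrics, so d, the baseline MCI-NC difference in SD units, is an assumption.

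**1. The plan's own figures.** Completers: 120 × (1 − 0.16) = 100.8, against about 100 stated. The stated AUROC power also reproduces, using the Hanley-McNeil variance, two-sided 5% and a null of 0.5 (my assumptions), if prediction is made within baseline strata:
- AUROC 0.86 for PDD, 24 v 6 among baseline MCI: 91.3% (stated 90%).
- AUROC 0.74 for MCI, 42 v 28 among baseline NC: 95.8% (stated 95%).
- With PDD against all others (24 v 76) the first figure would be about 100%.

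**2. Group sizes per 100 completers.**

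| Baseline | Progress | Do not progress |
|---|---|---|
| NC, 70 | 70 × 0.6 = 42 | 28 |
| MCI, 30 | 30 × 0.8 = 24 | 6 |

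The contrast is 28 always-normal v 42 + 24 = 66 progressors. The baseline MCI share is 0/28 = 0% against 24/66 = 36.4%. The 6 stable-MCI patients fall in neither group. Halving both conversion rates gives 49 v 33 with 18 left out, and the share is unchanged at 12/33 = 36.4%.

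**3. Spurious group difference.** Take a metric that differs by d between the baseline classes and is unrelated to progression within each. The expected difference is (24/66) × d = 0.364d, which is 0.18 SD at d = 0.5 and 0.29 SD at d = 0.8.

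**4. Rejection rates, if the t test uses these groups.** Simulation with 20,000 runs, 28 v 66:

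| d | Uncorrected 5% | Bonferroni over 6 metrics (nominal 0.8%) |
|---|---|---|
| 0.5 | 12% | 2.9% |
| 0.8 | 21% to 22% | 6.6% |

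The article states a correction but not its method. Bonferroni over the six listed topological features is used here for illustration.

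**5. The correlation, which is what the quoted sentence describes.** Among the 66 progressors let q = (24/66) × (42/66) = 0.231, and let g be the gap between classes on a cognitive subtest in SD. With no relation inside either class,

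r = q·d·g / √[(1 + q·d²)(1 + q·g²)].

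With g = 1.5 (an assumption), |r| is 0.14 at d = 0.5 and 0.21 at d = 0.8. Simulation finds it significant at an unadjusted 5% in about 20% and 41% of runs per subtest. With g = 1.0 the rates are about 13% and 25%.

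**6. After the fix.** Adjusting for baseline status in all 100, or comparing 42 with 28 among baseline NC only, returns the rejection rate to about 5% at every d tried (0 to 1.0). Precision does not suffer. The information on the progression effect is 42 × 28/70 + 24 × 6/30 = 16.8 + 4.8 = 21.6, against 28 × 66/94 = 19.7 for the pooled contrast.

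**The case against.** - **The groups belong to the correlation sentence.** The t-test sentence names none, and the only groups mentioned earlier in that section are PD and controls. This stands. A reader might infer that the planned t test is always-normal v progressors with a 12% to 21% false-positive rate. The article does not say so, and those rates ignore its multiplicity correction.
- **Pooling is inferred.** The progressor group is undefined, the power section lists the transitions separately, and the AUROC power fits within-stratum thinking. This also stands, but the power section calls both transitions conversion. If only NC converters were meant, MCI-to-PDD would have no place in this comparison and the wording would still need repair.
- **The sentence asks about association with cognition**, and a correlation arising from a mix of NC and MCI is partly a real one. That is fair. The difficulty is the grouping by progression, which invites a prognostic reading. Nor does it follow that the reference group would show no correlation, since cognition and topology vary among NC patients too.
- **Scans are annual.** A fixed MCI-NC offset cancels in within-person change, and the thinning hypothesis concerns a rate. This stands for change scores, but Connectivity Analysis describes none.
- **Wider effects.** A reader might extend the point to the cortical-thickness map or to the PDD prediction model. The text does not support this: the map's groups are unnamed, and nothing says this comparison selects predictors for the logistic model.
- **Few patients are lost.** About 6 in 100 are left out of this comparison, and they remain in the longitudinal cognitive model. They are nevertheless the only non-progressing comparators for MCI-to-PDD.

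**Conclusion.** The point holds in limited form. On the plain reading, the named groups confound baseline cognitive status with progression: 0% v 36% MCI at baseline, with about 6 of 100 completers in neither group. A topology-cognition association can then reflect existing impairment, and so can a group difference if the t test uses the same groups. The spurious group difference is 0.36d, or 0.18 to 0.29 SD for d of 0.5 to 0.8, with rejection at an unadjusted 5% in about 12% to 21% of tests per metric before the planned multiplicity correction. This rests on the plan's mix and conversion rates, on pooling as the plain meaning of an undefined label, on an assumed d, and on a metric analysed as a level and not as change. The documents do not show that a false marker will arise, only that this comparison could not distinguish one from a true marker.

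**What to change.** Define progression relative to baseline status: NC to MCI or PDD, and MCI to PDD. Relate each network metric to progression (yes/no) in one model of all completers, adjusted for baseline NC/MCI, with stable-MCI patients kept as non-progressors. Apply the same grouping and adjustment to the topology-cognition correlations, and name the groups for the t test. Report NC-to-MCI v NC-stable and MCI-to-PDD v MCI-stable as supporting contrasts.

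The cost is analysis wording only, with no new data. The limitation is that the within-MCI contrast is very small on the plan's figures (about 24 v 6), so the adjusted model should lead. That model assumes a common progression effect in both strata and draws most of its information from baseline NC patients (16.8/21.6 = 78%), which should be stated when it is reported.

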### Statistical Analysis and Power

A sample of 120 PD patients is planned for this study. On the basis of the experience of longitudinal studies in PD, the attrition (mortality and loss to follow-up) is anticipated at 16% for 4 years. Thus, initial recruitment of 120 patients will yield about 100 subjects after 4 years. On the basis of published data, we estimate 70% PD-NC and 30% PD-MCI patients in our sample, and conversion rates of 60% from NC to MCI and 80% from MCI to PDD after 4 years. One of our primary goals is to evaluate progression patterns to determine time-specific differences between groups (NC vs MCI at baseline and PDD vs MCI, MCI vs NC, and PDD vs NC at year 4). Our study will have 80% power to detect medium-to-large average differences across time between the different groups under various within-subject correlations. In terms of predictive models for 4-year outcomes, our study will have 90% power to detect at least 0.86 area under the receiver operating characteristics curve (AUROC) for PDD conversion and 95% power to detect at least 0.74 AUROC for MCI at year 4.

To study differential cognitive progression patterns, generalized estimating equations will be used for describing the longitudinal trajectories of neuropsychological and visuoperceptual performances between PD-NC and MCI groups comparing baseline performance with different time points. The model will provide estimates of PD-MCI versus PD-NC differences at specific time points and longitudinally. Covariates such as age, UPDRS, and visual illusions or hallucinations will be added to the model to enable determination of adjusted differences.

We will investigate the prognostic value of baseline cognition in predicting relative risk for progression to PDD through a multiple logistic regression model. The best combination of baseline measures and covariates included in the prediction model will be selected by the elastic net procedure. Summary statistics of the AUROC will be used to evaluate the predictive power. Sensitivity, specificity, positive predictive value, and negative predictive value will be calculated from the optimal threshold determined by the Youden index. The prediction models will be cross-validated by training and testing methodology.

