## Introduction

### Background

Parkinson disease (PD) is the second most common neurodegenerative disorder characterized by progressive movement deficits and is caused by degeneration of nigrostriatal dopamine neurons and deposition of α-synuclein in intraneuronal Lewy body (LB) inclusions [1]. Nonmotor features can characterize the earliest phase of the disease even before clinical motor impairment. Mild cognitive impairment (MCI) is a prominent nonmotor feature that is present early in the disease process and increases over time, eventually converting to dementia (Parkinson disease dementia [PDD]). Follow-up studies reveal that MCI is present in one-third of patients and progresses to PDD, with conversion greater than 80% after 15 to 20 years [2,3]. Prospective longitudinal studies demonstrate that PDD is common, with a 4-year prevalence 3 times higher than the general population [4,5]. However, dementia onset is variable, with a subset of patients demonstrating rapid conversion, resulting in significant disability and poor quality of life [4,6,7]. The neural and pathophysiologic mechanisms predicting rates of PD progression remain poorly understood and are key research priorities. Biomarkers signaling risk for PDD will facilitate intervention during early therapeutic windows, thus optimizing the chances of slowing progression.

Early cognitive deficits in PD have been characterized as executive and considered to be related to reductions in frontostriatal activity, suggesting a dopaminergic substrate [8]. However, characterization of MCI in early PD has revealed extensive deficits outside the executive domain and is not fully explained by dopamine depletion alone [9,10]. Therefore, identification of early reliable biomarkers that are predictive of risk for dementia conversion will require models of PD-MCI that focus on markers outside of the dopaminergic network. Widespread distribution of dopamine receptors in the neocortex is well recognized, with a rostrocaudal dopamine receptor gradient with the highest receptor densities in the prefrontal cortex and lowest densities in the occipital regions [11]. Therefore, biomarkers targeting posterior cortical changes may be more reliable for earlier prediction.

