Current studies looking at different types of biomarkers suggest different possible contributors to PDD, but findings have been inconsistent across studies [19]. Understanding the relationships between genetic risk factors for distinct pathologies and their resultant clinical presentation in PD is crucial for the development of disease-modifying interventions. Evaluating early cognitive deficits in PD and markers of future cognitive progression will shed light on whether PD pathology progresses in a consistent, expected pattern. Prospective longitudinal studies are essential to identify the initial cognitive symptoms and temporal pattern of atrophy and neural progression predictive of outcomes [7,20] *.* Thus, based on the models of pathological staging and anticipated sequence resulting in cognitive decline, accelerated cognitive progression may be reflected in biomarkers of early posterior cortical changes reflective of α-synuclein [12].

Cognitive profiles provide an index of staging of neuroanatomic regions, reflecting density and distribution of pathologic burden. Symptoms of visual hallucinations are associated with posterior cortical involvement and predict 75% conversion to PDD in 2.5 years, with widespread atrophy providing critical clues for biomarker identification [21]. Although visual hallucinations are specific to cognitive decline in PDD, they are not sensitive, given the low incidence of reporting by patients. Thus, the detection of associated visuoperceptual deficits may improve prediction of posterior cortical pathology and future cognitive decline.

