## Discussion

### Overview

Cardinal features of idiopathic PD include motor symptoms attributed to dopaminergic depletion of the dorsal striatum. Nonmotor features of the disease such as cognitive impairment are common early in the disease process and can dominate in advanced stages, creating significant disability and poor quality of life. Follow-up studies reveal that MCI is present in one-third of the patients and can progress at variable rates to PDD. After 15 to 20 years, more than 80% of patients with MCI are diagnosed with PDD [2]. However, the neural and pathophysiologic mechanisms underlying variable cognitive deficits and their progression in PD remain poorly understood. Cognitive profiles in nondemented early-stage PD can be widespread, extending beyond expected frontostriatal circuitry. Furthermore, DRT can have a paradoxical effect on attention and memory, with evidence for overdosing of nondepleted ventral striatal circuits early in the disease process, suggesting that these deficits may be unreliable predictors of cognitive progression [9,10]. PD-MCI is heterogeneous in clinical presentation (executive, memory, and visuospatial), reflecting the presence of extranigral pathology in addition to dopamine. The co-occurrence of LB inclusions (α-synuclein) and Alzheimer pathology (amyloid-β and tau) is essential for the development of PDD, but the neurobiological basis of PD-MCI is unknown. Density of amyloid-β is predictive of neocortical atrophy, but how the predominate pathology in PDD (α-synuclein) influences clinical features or signals conversion to dementia is unclear.

Our central hypothesis, based on models of pathologic staging, is that earlier involvement of posterior cortical regions and the dorsal and ventral visual pathways (with or without the presence of visual hallucinations) are reliable markers for future cognitive progression. Our strategy toward this overarching goal is to characterize cognitive, genetic, and neural network progression in PD over a 4-year period. This allows evaluation of variable timing of onset and accelerated rates of cognitive progression, reflecting a deviation from expected stages of progression. Prospective longitudinal studies are essential to identify the initial cognitive symptoms and temporal pattern of atrophy and neural progression predictive of outcomes. These studies have been lacking, with overreliance on cross-sectional motor and pathological dementia studies in PD [7,20].

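### The power section assumes that 80% of PD-MCI patients convert to dementia in 4 years, which does not fit the article's own 15-to-20-year figure; the power for the PDD contrasts is probably overstated

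*Protocol article*

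**What the plan says.** All references are to the protocol article.

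- **Statistical Analysis and Power, sample:** "A sample of 120 PD patients is planned for this study"; "the attrition (mortality and loss to follow-up) is anticipated at 16% for 4 years"; "initial recruitment of 120 patients will yield about 100 subjects after 4 years". The baseline mix is taken as 70% PD-NC and 30% PD-MCI.
- **Same section, conversion:** "conversion rates of 60% from NC to MCI and 80% from MCI to PDD after 4 years". The rates are credited to published data, with no reference at that point.
- **Same section, power:** "Our study will have 80% power to detect medium-to-large average differences across time between the different groups under various within-subject correlations". The contrasts named under a primary goal include PDD vs MCI and PDD vs NC at year 4. The section also states 90% power at an AUROC of 0.86 for PDD conversion and 95% power at 0.74 for MCI.
- **Introduction, Background:** "MCI is present in one-third of patients and progresses to PDD, with conversion greater than 80% after 15 to 20 years".
- **Discussion, Overview:** "After 15 to 20 years, more than 80% of patients with MCI are diagnosed with PDD". Here the denominator is explicitly patients with MCI.
- **Introduction, Background, on visual hallucinations:** these symptoms "predict 75% conversion to PDD in 2.5 years". The Abstract treats such patients as a subgroup.

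**The concern.** The same transition reaches about the same proportion in 4 years in the power section and in 15 to 20 years elsewhere, and nothing explains the difference. The rest of the text does not point to a fast-converting cohort. The Background confines rapid conversion to a subset of patients, and entry is limited to minimal or mild disease without dementia.

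The 80% sets the size of the year-4 PDD group. If it is too high, that group is smaller than planned, and the claimed power for PDD vs MCI and PDD vs NC is too favourable.

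**Working it through.** **1. Year-4 groups from the plan's inputs.** 120 × 0.84 = 100.8, so about 100 completers: 70 NC and 30 MCI at baseline.

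- PDD: 30 × 0.80 = 24, leaving 6 still MCI.
- New MCI: 70 × 0.60 = 42, so MCI = 42 + 6 = 48.
- NC: 70 − 42 = 28.

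**2. Reproducing the stated AUROC power.** The article gives neither null value nor alpha; I assume a null of 0.5 and two-sided 0.05. Power = Φ[(A − 0.5 − 1.96·SE₀)/SE₁], with SE₀ = √[(n₁+n₀+1)/(12·n₁·n₀)] and SE₁ the Hanley-McNeil standard error at A.

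- PDD, 24 vs 6, A = 0.86: SE₀ = 0.134, SE₁ = 0.0716, so Φ[(0.36 − 0.2625)/0.0716] = 0.91 (stated: 90%).
- MCI, 42 vs 28, A = 0.74: 0.96 (stated: 95%).

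Both agree, so the stated power very probably rests on the 80% and 60% rates.

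**3. What the long-run figure implies at 4 years.** Under a constant hazard, if a proportion R has converted by T years, the 4-year proportion is 1 − (1 − R)^(4/T).

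| Long-run figure | 4-year rate | PDD of 30 |
|---|---|---|
| 80% at 20 years | 1 − 0.2^(4/20) = 28% | about 8 |
| 80% at 15 years | 1 − 0.2^(4/15) = 35% | about 10 |
| 90% at 15 years | 1 − 0.1^(4/15) = 46% | about 14 |
| 95% at 15 years | 1 − 0.05^(4/15) = 55% | about 16 |

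In reverse, 80% at 4 years gives 1 − 0.2^(15/4) = 99.8% at 15 years.

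**4. Detectable differences.** Two-sample t test, two-sided 0.05, 80% power. NC stays at 28; MCI = 72 − PDD. For a mean of four visits with within-subject correlation ρ, the single-visit value is multiplied by √[(1 + 3ρ)/4], which is 0.791 at ρ = 0.5 and 0.689 at ρ = 0.3. Values are in SD.

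| PDD / MCI / NC | PDD vs NC: year 4 | mean, ρ 0.5 | mean, ρ 0.3 | PDD vs MCI: year 4 | mean, ρ 0.5 | mean, ρ 0.3 |
|---|---|---|---|---|---|---|
| 24 / 48 / 28 (plan) | 0.79 | 0.63 | 0.55 | 0.71 | 0.56 | 0.49 |
| 16 / 56 / 28 | 0.90 | 0.71 | 0.62 | 0.81 | 0.64 | 0.56 |
| 14 / 58 / 28 | 0.94 | 0.74 | 0.65 | 0.85 | 0.67 | 0.58 |
| 10 / 62 / 28 | 1.06 | 0.84 | 0.73 | 0.97 | 0.77 | 0.67 |
| 8 / 64 / 28 | 1.16 | 0.91 | 0.80 | 1.07 | 0.84 | 0.73 |

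For a true difference of 0.8 SD in PDD vs NC, single-visit power falls from about 80% with 24 PDD to 49-56% with 8-10. On the four-visit mean at ρ = 0.5 it is 69-76%.

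**5. AUROC power with fewer converters.** Same formula, A = 0.86, among the 30 MCI patients: 16 vs 14 gives 0.98, 10 vs 20 gives 0.95, 8 vs 22 gives 0.92, 6 vs 24 gives 0.83 and 5 vs 25 gives 0.76.

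**The case against.** **The background gives only a lower bound.** More than 80% at 15 to 20 years does not logically exclude 80% at 4 years. The Background also calls dementia onset variable, and heterogeneity brings conversions forward, so a constant hazard may understate the 4-year rate. The cited literature might contain a 4-year figure. All this stands: the documents fix no replacement value, and 28-35% cannot be presented as the article's own rate. It does not explain why the power section differs so far from the background.

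**The power claim concerns averages across time.** This also stands. The 1.06-1.16 SD and 49-56% figures describe a single visit. At correlation 0.3 the averaged differences stay at or below 0.80 SD even with 8 PDD patients, which could still be called medium to large. No numerical effect size is stated against which the claim could fail outright.

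**A reader might infer that the PDD prediction model loses power too.** The calculation does not support that. The planned split of 24 vs 6 is limited by its 6 non-converters; with 8-10 converters the smaller class is larger, and power is 92-95%. It falls clearly below 90% only at about 6 converters or fewer. The baseline NC vs MCI comparison does not depend on PDD conversion at all.

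**The plan can recruit again in year 3 to secure enough converters** (Methods, Overview). The trigger is MRI-related attrition or failure to return, not low conversion, and late recruits would have shorter follow-up within the 5-year project. This is partial mitigation at most.

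**Conclusion.** The point holds in a limited form. The 4-year rate in the power section is unreferenced and out of step with the article's own long-run figure. The plan's arithmetic is otherwise sound, so this is a questionable planning input and not a calculation error.

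Under the constant-hazard assumption, with long-run conversion of 80-95%, the year-4 PDD group is about 8-16 and not 24. The power for PDD vs MCI and PDD vs NC is then overstated. The loss is marked at year 4 itself, real for four-visit averages at correlation 0.5, and modest at 0.3.

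The inconsistency is certain; its size is not, because it depends on the assumed hazard, the long-run proportion and the within-subject correlation. The documents do not support extending the finding to the stated AUROC power or to the baseline comparison.

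**What to change.** In Statistical Analysis and Power:

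1. Reconcile the 4-year MCI-to-PDD rate with the Background and Discussion, either by citing a 4-year source that fits this early, mild cohort or by lowering the rate.
2. State the expected year-4 numbers of NC, MCI and PDD patients over a range of conversion rates, for example 28% to 80%.
3. Give the detectable PDD vs MCI and PDD vs NC differences in SD units over the same range, at year 4 and averaged over visits, with the within-subject correlations named.

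The primary objective need not change and no further patients are required. The cost is a rewritten power paragraph and less favourable stated detectable differences for the PDD contrasts.
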